### **4.9. Secondary safety outcome analyses: temperature**

Temperature analysis will be performed in the neonatal strata only.

A summary table will be presented for all babies randomised to treatment groups:

- Temperature at baseline: mean (SD) [N]
- Temperature pre-application at all time points: mean (SD) [N]
- Temperature at post-application at all time points: mean (SD) [N]

#### **Temperature analysis**

- The analysis will include all babies randomised to treatment with at least one antiseptic application. Babies in the SOC group will be excluded from the analysis.
- The outcome variable will be:
  - Change in temperature from pre to post application.
- Fixed effects in the model will be:
  - Antiseptic (1% CHG, 2% CHG, OCT)
  - Frequency of application (once, multiple)
  - Day of trial (continuous; mfp will be used to assess linearity)
  - Temperature pre application (continuous; mfp will be used to assess linearity)
- Individual will be fitted as a random effect to account for repeated measures within individuals.
- Normally distributed errors will be fitted.
- Comparison of main effects within arms will be assessed using the estimate and 95% confidence interval of the comparison of differences between factors and in comparison, to SOC.
- The reference group will be 1% CHG once only as it is the most straightforward and conservative to implement. The SOC will not be used as the reference as the sample size for this arm is lower than for the factorial arms.

Additional analyses, as per the primary outcomes, may also be performed.

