### **Neonatal participants in control group:**

Temperature: Temperature will be recorded at baseline and once daily before the swabs thereafter until discharge or 72 hours.

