##### **Neonates:**

Safety will be assessed using a modified skin score which assesses the skin condition, and presence of erythema, dryness, and any other sign of skin damage (see [Appendix I](#))(46,47). This will be performed before each application of antiseptic and 30 minutes after application. The skin score will be considered as both an absolute value and graded. Skin score assessments will be performed once every day on all babies to provide unbiased comparisons across randomised groups.

Temperature will be monitored before and 15 minutes post every antiseptic application. For neonates in the once only and control arms temperature will be measured daily. Guidelines for repeating the temperature if it is out of range will be outlined in the clinical MOP.

Hypothermia will be graded as follows:

- Grade 1: 35.5 - 36.0C
- Grade 2: 35.4 - 35.0C
- Grade 3: 34.0 - 34.9C
- Grade 4:  $<34.0C$

Other adverse events will be monitored for daily and reported as described in [Section 5](#).

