#### **4.10. Secondary safety outcome analyses: AEs and SAEs**

SAEs and AEs will be presented overall and split by MedDRA System Order Class (SOC) and Preferred Term (PT). AEs and SAEs will be displayed as n(%)M where M is the number of events experienced for all children experiencing at least one event ( $M > n$ ).

- SAEs: n(%)M
- Antiseptic related SAEs: n(%)M
- Grade 3 or 4 AEs: n(%)M
- Grade 3 or 4 skins scores (appendix I and II of protocol) : n(%)M
- Grade 3 or 4 hypothermia in neonates only (section 4.7.3 of protocol) : n(%)M

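### SAP 4.9 promises a temperature comparison with standard of care that its model cannot estimate, and its frequency term says nothing about repeat application

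*Protocol*

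**What the plan says.** Temperature is a neonatal secondary safety outcome, defined as change in absolute temperature and hypothermia grade (Protocol 4.10.2.2, SAP 2.2).

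SAP 4.9 sets the outcome as "Change in temperature from pre to post application". The fixed effects are antiseptic, frequency (once or multiple), day of trial as a continuous term with mfp to check linearity, and pre-application temperature. Individual is a random effect. Only babies randomised to antiseptic with at least one application enter: "Babies in the SOC group will be excluded from the analysis". The same list then says main effects will be assessed by the "comparison of differences between factors and in comparison, to SOC". It adds that SOC is not the reference because that arm is smaller, a reason that would matter only if SOC were in the model. The summary table in 4.9 is limited to babies randomised to treatment groups.

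The measurement schedule is in Protocol 4.7.1.2 and 4.7.3:

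- Single arms: before and 15 minutes after the one application, then once daily.
- Multiple arms: before and 15 minutes after every application, at baseline, 24, 48 and 72 hours or discharge.
- Control: "Temperature will be recorded at baseline and once daily before the swabs thereafter until discharge or 72 hours".

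SAP 4.10 separately tabulates Grade 3 or 4 hypothermia, which Protocol 4.7.3 defines as below 35.0 °C.

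**The concern.** There are two faults in a stated analysis and one gap beside it.

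1. The SOC comparison is promised for a model that contains no SOC babies and whose outcome does not exist for them.
2. The frequency coefficient looks like an estimate of the effect of repeated application on temperature. It is not, because the single arms give before/after data only at the first application.
3. All seven arms have daily temperatures, but no stated analysis models them or compares them with SOC.

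The Protocol (6.2.1) names hypothermia after chlorhexidine cleansing as a risk and gives safety as a main reason for the pilot. Frequency is one of the two factors on which a regimen will be chosen. A near-zero frequency coefficient with a confidence interval could be quoted as evidence that repeats add no temperature risk, although the model cannot address that question.

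**Working it through.** **The plan's own figure.** The documents give no power or effect size for temperature. The nearest figure is for log CFU: 90% power for 0.58 SD between frequencies, two-sided α = 0.05, with 3 × 21 = 63 babies per frequency. Check: 0.58/√(2/63) = 3.255; 3.255 − 1.960 = 1.295; Φ(1.295) = 0.902. It reproduces, and confirms 63 v 63 as the intended frequency comparison.

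**Before/after pairs available to the 4.9 model, full follow-up**

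| | Day 0 | Days 1–3 | Total |
|---|---|---|---|
| Single (63 babies) | 63 | 0 | 63 |
| Multiple (63 babies) | 63 | 3 × 63 = 189 | 252 |
| SOC (21 babies) | 0 | 0 | 0 |
| All | 126 | 189 | 315 |

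SOC supplies 0 of 315 pairs, so no SOC contrast exists. Single arms supply 0 of the 189 later pairs.

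**What the frequency coefficient estimates.** Single-arm data sit only on day 0, and frequency has its own parameter. The day term is therefore fitted from the multiple arms alone. The frequency coefficient is the multiple arms' fitted value at day 0 minus the single arms' day-0 mean. Leave aside the antiseptic and pre-application terms, which are balanced by randomisation on day 0. Suppose the fall is larger by a constant d at every application after the first, so the multiple arms' extra change on days 0 to 3 is 0, −d, −d, −d.

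- *Categorical day:* the fitted day-0 value is 0, so the coefficient is 0 (0% of d).
- *Linear day:* mean = −0.75d. Slope = [(−1.5)(0) + (−0.5)(−d) + (0.5)(−d) + (1.5)(−d)]/5 = −0.3d. Fitted day-0 value = −0.75d − 1.5(−0.3d) = −0.30d (30% of d). This is purely the error of forcing a step onto a straight line.

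If instead the fall deepens by the same amount at each application (0, −d, −2d, −3d), the line fits exactly and the coefficient is 0 even with linear day.

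**Simulation of the listed model** (REML, random intercept, 100 runs per scenario; assumed between-baby SD 0.2 °C and residual SD 0.3 °C):

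| Assumed truth | Day term | Mean frequency coefficient |
|---|---|---|
| Fall deepens 0.3 °C per application | linear | −0.005 (SE 0.06) |
| Extra 0.5 °C after the first | categorical | 0.002 |
| Extra 0.5 °C after the first | linear | −0.15 (30%) |
| Extra 0.5 °C after the first, 60% stay each day | linear | −0.087 (17%) |

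An SE of about 0.06 gives an interval of roughly ±0.12 °C, which would look precise.

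**Scheduled temperature readings per baby who stays 72 hours:** multiple 4 before + 4 after = 8; single 1 + 1 + 3 daily = 5; SOC 1 + 3 daily = 4. Readings 15 minutes after application exist only in the active arms.

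**Where SOC temperature is used.** The general rule in SAP 4 shows SOC separately unless stated otherwise, but the 4.9 table states treatment groups only. That leaves the Grade 3 or 4 count in 4.10. Grades 1 and 2 (35.0 to 36.0 °C) are not compared with SOC in any stated analysis.

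**The case against.** A reader might infer that the plan gives false reassurance on hypothermia, or that it cannot detect harm from repeat application. The documents do not support either. SAP 4.9 tabulates pre- and post-application temperature at all time points, and 4.10 tabulates Grade 3 or 4 hypothermia. The day term carries the repeat-application signal, though mislabelled and mixed with age. SAP 4 rules out significant/not significant conclusions, and serious adverse reactions go to the DMC in real time. Gross harm could be seen. What stands is narrower: the coefficient is uninformative about repeats and open to misreading.

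Leaving SOC out of a before/after model is right, since controls have no application; the error is the promised comparison. Before/after change also suits the stated hazard of cooling after cleansing, and day 0 offers up to 126 babies for the antiseptic contrasts. A daily reading about 24 hours after the last application answers a different question, so it should be added and not substituted.

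The 8, 5 and 4 readings are maxima cut short by discharge, so a twofold difference in ascertainment is an upper bound. The size of any extra fall is assumed, and because mfp will be used a linear day term is not fixed. These points limit the illustration but leave the structural fault.

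SAP 4.9 also allows additional analyses as for the primary outcome. These are optional, and a frequency-by-timepoint interaction could not help: the single arms have no pairs after day 0.

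**Conclusion.** The point holds. The SOC comparison in SAP 4.9 cannot be estimated, and this follows from the text alone. The frequency coefficient compares identical first applications. Under full follow-up and a constant extra fall after the first application, it recovers about 0% of that fall with categorical day and about 30% with linear day, the latter only through misfit. These percentages illustrate a mechanism; no document supplies a true effect.

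The daily temperatures have no stated model, and the one specified use of SOC temperature rests on unequal scheduled readings. The antiseptic contrasts in the before/after model remain valid.

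Severity is moderate: a secondary safety outcome in a pilot, with no effect on the primary analysis or sample size.

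**What to change.** In the before/after model of SAP 4.9:

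- Delete the comparison with SOC and the sentence explaining why SOC is not the reference.
- Replace the frequency term with application number. It coincides with day unless an application is missed, so it should stand in for the day term too. Report change by application number descriptively for the multiple arms, noted as confounded with postnatal age.

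Add:

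- A mixed model of daily pre-swab temperature at 24, 48 and 72 hours in all seven arms including SOC, adjusted for baseline temperature. Take the frequency contrast at 48 and 72 hours: readings precede application, so at 24 hours both schedules have still had only one. State the caveat that babies leave by discharge.
- A comparison of hypothermia Grades 1 to 4 between arms on these common daily readings, with 15-minute post-application grades shown separately for the active arms.

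The cost is a change of SAP wording and one extra model on data already collected. The downside is limited numbers at 48 and 72 hours because of discharge.

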#### 4.5.1.1. Patient inclusion criteria

*Mothers:*

1. Presenting in labour with or without rupture of membranes

*Neonates:*

1. Born in a healthcare facility
2. Postnatal age at randomisation <24 hours
3. Birth weight >1000g

**4.5.1.2. Patient exclusion criteria***Mothers:*

1. Under the age of 18 (minor in Malawi)
2. Any contra-indication to digital vaginal examination
3. In active labour (regular contractions and/or cervical dilatation of more than 4cm)
4. Poor perineal and vaginal skin condition as judged by clinician
5. Planned elective caesarean-section delivery
6. Known or suspected allergy to chlorhexidine or octenidine or phenoxyethanol
7. Intrauterine death confirmed or expected before randomisation
8. Antiseptic application or enrolment in the trial determined inappropriate in the opinion of the enrolling clinician
9. Any recent or planned (within 4 hours) iodine application to the perineum or vagina
10. Unable to obtain consent

*Neonates:*

1. Born by planned elective caesarean section
2. Born to mothers recruited in the trial
3. Poor skin condition (skin score of 2 or more in any of three domains (see [Appendix I](#))) at the time of enrolment
4. Known congenital or acquired skin disorder or defect at time of enrolment
5. Antiseptic application or enrolment in the trial determined inappropriate in the opinion of the enrolling clinician
6. Any recent or planned (within 4 hours) iodine application to body
7. Any planned or previous lumbar puncture
8. Unable to obtain parental or guardian consent

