#### **4.6.2.1.2. Neonatal strata**

CHG is used in neonatal units (NNUs) in concentrations from 0.2-4%(40–43). Previous large- scale studies of CHG to decolonise neonatal skin have used concentrations towards the lower end of the range(22); however babies born in LMIC with high levels of environmental contamination may require relatively high concentrations to achieve effective decolonisation. This study will use an upper limit of 2% CHG because of rare reports of skin damage with concentrations of CHG  $\geq 2\%$ , although these are mostly limited to infants <1000g at birth(44). This trial is only recruiting neonates with a birth weight >1000g. OCT 0.1% and 0.1% Octenidine 2% Phenoxyethanol (OHP) are the standard antiseptics in neonatal unit's in Germany and there are published data on safety in neonates(16), including premature newborns(45). This study of OHP in premature newborns also demonstrated that although phenoxyethanol undergoes cutaneous absorption, it almost completely metabolizes to 2-phenoxyacetic acid, which can be detected in the urine. As with the maternal strata, OHP will be tested at a single concentration because of limited published data.

Previous studies from high income countries have documented a significant decline in skin bacterial load for up to 48 hours following a single topical application of CHG(14), however infants from LMIC may be exposed to high levels of environmental contamination during birth and in the postnatal period. This study will therefore compare a single antiseptic application to 24 hourly repeat applications until discharge, up to a maximum of 72 hours. Twenty-four hourly applications were selected as the maximum feasible to scale up in a LMIC setting. A control arm receiving standard of care will also be recruited.

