#### **4.6.2.3. Neonatal treatment**

The antiseptic will be applied topically to the whole body with the same volume of CHG/OHP, excluding the face to avoid the eyes.

Before an antiseptic is applied, the neonate's temperature will be measured and the skin condition score assessment will be performed. Whilst treatment is being applied, precautions should be taken to keep the baby warm and also to avoid pooling of the antiseptic around the baby. After the application, the neonate should be re-dressed and their body temperature will be measured after 15 minutes. The neonate should be observed for skin reactions at 30 minutes after each application.

In the case of rare and highly unlikely accidents such as splash injury to the eye from antiseptic, flush the affected area with copious saline as quickly as possible and inform the local paediatric services. See MOP for further details.

The normal bathing, washing and cord care regime delivered by the nursing staff or family will be permitted.

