| Swabs (peri-rectal/rectal and cervical/neck)                 |           |               | X            | X | X | X |           |
| Antiseptic application                                       |           |               | X            | X | X | X |           |
| Participants in control group                                |           |               |              |   |   |   |           |
| Clinical assessment (temperature, skin score + AE)           |           |               | X            | X | X | X |           |
| Swabs (peri-rectal/rectal and cervical/neck)                 |           |               | X            | X | X | X |           |

Eligibility will be checked by trial staff. Parents/carers of neonates who meet all of the inclusion and none of the exclusion criteria will be provided with a participant information sheet, have the trial verbally explained and given the opportunity to have their questions answered. Informed consent will be recorded (Section 4.5.3).

An enrolment form will be completed and data entered into the database. Participants will be randomised (details in [Section 4.5.5.1](#)) and have baseline data collected, including antenatal history, estimated gestational age, birth weight, labour duration, mode of delivery, co-morbidities, and intrapartum and postpartum antibiotic history.

Assessment and treatment regime will be according to allocation:

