#### **4.10.4. Analysis plan (brief)**

The analyses will be described in detail in a full Statistical Analysis Plan. This section summarises the main issues.

The primary analysis population is intention-to-treat, including all randomised participants, regardless of treatment received. This corresponds to estimating the impact of the effectiveness of the treatments. However, in secondary analyses we will also use inverse-probability weighting methods to adjust for deviation from randomised strategy, which is a more efficient approach than defining a per-protocol population.

Analysis of the co-primary endpoints will compare within-individual differences over time across randomised arm to maximise the information gained from the trial. Analysis will use linear mixed-models, with individual as a random effect, will adjust for baseline values of each outcome, and use Normally distributed errors. Analysis will be both frequentist, enabling straightforward comparison between arms (primary analysis since sample size is based on this), and Bayesian, enabling estimation of the probability that one arm is truly superior to another. This is more powerful when sample sizes are small as use of priors provides additional information. Sensitivity analysis to prior assumptions will be performed using optimistic, non-informative and sceptical priors.

The effect of each treatment arm will be assessed within a single model with each factor being fitted independently as a factor, and not as a continuous variable. Comparison of main effects within arms will be assessed using the estimate and 95% confidence interval of the comparison of differences between factors and in comparison, to control. As this is a pilot trial, the sample size was not powered to robustly detect interactions between treatment and frequency and so we will not test these formally, but will use exploratory analyses to assess whether there is any evidence supporting individual interactions testing each one, one at a time.

Similar mixed models will be used to analyse change in skin temperature after vs before each application, including individual as a random effect, the change in temperature as the outcome and the pre-application (baseline) temperature as a factor.

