### 6.2. Ethical conduct

#### 6.2.1. Ethical considerations

By necessity this trial recruits potentially vulnerable groups (labouring women, neonates). Every care will be taken to respect women and newborns at this time and to ensure that recruitment and participation does not interfere with clinical care.

The autonomy of women and parents/carer's will be protected throughout the trial and during the informed consent process. Risk of coercion will be reduced by separating the role of the clinical team and the researchers, with the clinical team acting as advocates for their patients. Care will be taken to gain and record written informed consent at an appropriate time before enrolment. Before consent is obtained, women and parents/carers will be fully informed of known risks and possible benefits by a participant information leaflet, and this will be reinforced by discussions with the trial research team. Additionally, the woman and their partner will have opportunity to discuss the study and have any questions answered. Women who are already known to be in active labour will not be approached by the research midwife, and will not be eligible for inclusion. Further information is in Section 4.5.3 ([Section 4.5.3](#)).

Antiseptic and swabs will be administered by trial staff at the time of planned vaginal examinations to minimise interruption to clinical care. Condition of the external mucous membranes will be examined prior to administration and antiseptic will not be applied if they are damaged or inflamed or if the participant has reported any severe side effects.

One ethical concern in this trial relates to potential skin or mucous membrane damage. Antiseptics, including CHG and OHP, are widely used for skin disinfection in neonates and mothers and are typically well tolerated. The main risk is with high concentrations (>2%) in extremely low birth weight/preterm neonates (<1kg/<28 weeks), among whom skin reactions have been observed, particularly when chlorhexidine is combined with alcohol. Hypothermia has also been observed after skin cleansing with chlorhexidine on the first day of life. This trial will exclude neonates less than 1kg at enrolment which will minimise, although not entirely eradicate these risks. However, close and regular monitoring of the

skin with a standardised skin condition scoring system, and temperature checking after application will allow chlorhexidine to be discontinued at the discretion of the local clinician.

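### Birth weight is collected and sets the neonatal entry limit, yet no prespecified analysis or baseline table uses it; adding it to the two neonatal safety models is a cheap, modest gain

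*Protocol*

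**What the plan says.** Protocol 4.5.1.1 makes "Birth weight >1000g" a neonatal inclusion criterion. Protocol 4.6.2.1.2 explains the cap on chlorhexidine concentration by rare reports of skin damage, "although these are mostly limited to infants <1000g at birth". Protocol 6.2.1 states: "The main risk is with high concentrations (>2%) in extremely low birth weight/preterm neonates (<1kg/<28 weeks), among whom skin reactions have been observed". The same section adds that combination with alcohol aggravates the skin risk and that hypothermia has been seen after cleansing on the first day of life. It says that excluding babies under 1 kg lowers these risks without removing them.

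Protocol 4.7.1.2 lists the neonatal baseline items, among them "antenatal history, estimated gestational age, birth weight, labour duration, mode of delivery".

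On analysis, protocol 4.10.4 describes a mixed model for temperature with "the change in temperature as the outcome and the pre-application (baseline) temperature as a factor". SAP 4.9 gives the fixed effects in full: antiseptic, frequency, day of trial, and "Temperature pre application (continuous; mfp will be used to assess linearity", with individual as a random effect. SAP 4.8 runs the skin score through the primary-outcome model, with baseline skin score replacing baseline log CFU. The neonatal baseline list in SAP 4.2 and the neonatal subgroup list in SAP 4.6 both include estimated gestational age. Neither includes birth weight.

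**The concern.** Protocol 6.2.1 gives safety as one of the main reasons for the pilot, which is meant to find a regimen that is both safe and effective for a later, larger trial. The protocol uses weight as its safety limit and concedes that the limit leaves some risk, so one expects the safety analysis to describe and examine weight among the babies enrolled. No planned analysis does so.

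Two things are lost. First, a baseline variable that may predict temperature change or skin score is left out of the models, so the safety intervals may be somewhat wider than they need be. Second, there is no planned report of how many babies near 1 kg were studied, or of how they fared. SAP section 4 flags baseline imbalance between randomised groups at p<0.05 for the variables it presents. Birth weight is not among them, so with 21 babies per arm a chance imbalance in it would not be flagged.

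**Working it through.** **Where birth weight appears**

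- Entry limit: protocol 4.5.1.1, repeated in SAP 1.2. Present.
- Baseline data collection: protocol 4.7.1.2. Present.
- Neonatal baseline table: SAP 4.2. Absent.
- Subgroups: SAP 4.6. Absent.
- Skin-score model: SAP 4.8. Absent.
- Temperature model: protocol 4.10.4 and SAP 4.9. Absent.

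**Inputs.** There are 21 babies per group (protocol 4.5, SAP 2.4), so the factorial margins are 2 × 21 = 42 per antiseptic and 3 × 21 = 63 per frequency. The stated 90% power is for 0.82 SD between antiseptics (two-sided alpha 0.012) and 0.58 SD between frequencies (alpha 0.05). These figures are for the primary endpoint; none is given for the safety models. The correlation r of birth weight with a safety outcome, given the other covariates, is not in the documents; 0.1 to 0.5 is assumed. The share q of small babies is not given either; 10% to 50% is assumed.

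**The plan's own figures first.** Normal approximation, SD = 1, one value per baby:

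- Antiseptics: SE = √(2/42) = 0.2182. Detectable at 90% power = 3.794 × 0.2182 = 0.828 SD; power at 0.82 SD is 0.894.
- Frequencies: SE = √(2/63) = 0.1782. Detectable at 90% power = 0.578 SD; power at 0.58 SD is 0.902.

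Both agree with the stated 90% within a point.

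**Effect of adding birth weight.** The SE is multiplied by √(1 − r²):

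| r (assumed) | √(1 − r²) | SE reduction | Antiseptics, detectable at 90% | Frequencies, detectable at 90% |
|---|---|---|---|---|
| 0.1 | 0.995 | 0.5% | 0.824 SD | 0.575 SD |
| 0.2 | 0.980 | 2.0% | 0.811 SD | 0.566 SD |
| 0.3 | 0.954 | 4.6% | 0.790 SD | 0.551 SD |
| 0.4 | 0.917 | 8.3% | 0.759 SD | 0.529 SD |
| 0.5 | 0.866 | 13.4% | 0.717 SD | 0.500 SD |

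**Birth weight by treatment interaction.** SE = √(2/(nq) + 2/(n(1 − q))). At 80% power and two-sided alpha 0.05 the multiplier is 1.960 + 0.842 = 2.802. For two antiseptics with q = 20%, there are 42 × 0.2 = 8.4 small babies per antiseptic, SE = √(2/8.4 + 2/33.6) = 0.5455, and the detectable interaction is 2.802 × 0.5455 = 1.53 SD.

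| q (assumed) | Two antiseptics | Two frequencies |
|---|---|---|
| 10% | 2.04 SD | 1.66 SD |
| 20% | 1.53 SD | 1.25 SD |
| 50% | 1.22 SD | 1.00 SD |

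**The case against.** The strongest reply is that this is a preference about covariates and not an error. Protocol and SAP agree on pre-application temperature as the adjustment, nothing promises an analysis by birth weight, and randomisation keeps the comparisons unbiased without it. That stands, and it limits the point to an improvement.

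Three stronger readings are tempting, and the documents support none of them.

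- A reader might infer that birth weight is the only risk factor the protocol names. Protocol 6.2.1 also names concentration, prematurity and alcohol, and ties hypothermia to the first day of life. Of these, chlorhexidine concentration is randomised, gestational age is a listed subgroup, and day of trial is in the temperature model. The skin reports mostly concern babies under 1000 g, who are excluded, so the documents show a residual risk above the limit and no weight gradient.
- A reader might infer that the plan is unable to show whether small babies fare worse. SAP 4.8 follows the primary-outcome analyses and can be read to bring the gestational-age subgroup with it. SAP 4.9 permits such additional analyses for temperature. Birth weight is also in the data set. What is missing is a prespecified analysis by birth weight itself.
- A reader might infer from "applied topically to the whole body with the same volume of CHG/OHP" that every baby gets one fixed volume, so that exposure per kg rises as weight falls. The phrase may equally mean equal volumes of the two products, and the section refers to the manual of procedures, which is not available. The point does not rest on it.

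It is also fair to say that safety monitoring of individual babies does not depend on this covariate. Temperature and skin are checked around each application (protocol 4.7.3), and SAP 4.10 tabulates grade 3 or 4 skin scores and hypothermia.

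**Conclusion.** The point holds as a low-cost improvement. Birth weight is collected, sets the entry limit, and is one of several factors linked to skin damage, with residual skin and hypothermia risk acknowledged above 1 kg. Yet it is absent from the neonatal baseline table, the subgroup list and both neonatal safety models. The arm comparisons remain unbiased.

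The gain in precision is probably modest: 0.5% to 4.6% of the SE for r of 0.1 to 0.3, and 8.3% to 13.4% only if r is 0.4 to 0.5. These figures rest on an assumed r and on one value per baby. With repeated measures, birth weight can explain only between-baby variation.

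The missing description of birth weight is the firmer part, because it depends on no assumption. An interaction test would not settle whether small babies respond differently: over the assumed range of q it detects only differences of 1.00 to 2.04 SD, and protocol 4.10.4 already says the pilot was not powered even for treatment-by-frequency interactions.

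**What to change.** In the SAP:

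- 4.2: add birth weight to the neonatal baseline list, so that the p<0.05 imbalance check covers it.
- 4.8 (neonatal stratum) and 4.9: add birth weight as a continuous fixed effect, alongside the existing covariates.
- 4.10: tabulate hypothermia and skin grades by birth-weight band, descriptively, with the bands fixed before database lock.
- If an interaction of birth weight with antiseptic or frequency is fitted, label it exploratory and report the estimate and interval without a claim of power.

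The cost is a few lines of SAP text and one degree of freedom per model with a linear term. No new data are needed.
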